## Abstract

**Background:**

Recent trials have revealed that sodium-glucose co-transporter 2 inhibitors (SGLT2-i) are effective against hyperglycemia and also reduce micro- and macro-vascular complications in patients with type 2 diabetes mellitus (T2DM). Most of the beneficial cardiovascular effects have been investigated in patients with heart failure and coronary artery disease (CAD). Yet, few human studies have been conducted to investigate the molecular mechanisms underlying these clinically beneficial effects in patients with CAD. Accordingly, the EMPA-CARD trial was designed to focus on the molecular effects of empagliflozin in patients with T2DM and CAD.

**Methods:**

In this multicenter, triple-blind randomized controlled trial, patients with documented known T2DM and CAD will be recruited. They will be randomized on a 1:1 ratio and assigned into two groups of empagliflozin 10 mg/daily and placebo. The primary endpoint is the effect of empagliflozin on changes of plasma interleukin 6 (IL-6) after 26 weeks of treatment. The secondary endpoints will consist of changes in other inflammatory biomarkers (Interleukin 1-beta and high-sensitive C-reactive protein), markers of oxidative stress, platelet function, and glycemic status.

**Discussion:**

The EMPA-CARD trial mainly tests the hypothesis that SGLT2 inhibition by empagliflozin may improve inflammatory status measured as reduction in inflammatory biomarkers in patients with T2DM and CAD. The results will provide information about the underlying mechanisms of SGLT2 inhibition that mediate the beneficial effects of this medication on clinical outcomes.

***Trial registration*:**

Iranian Registry of Clinical Trials. www.IRCT.ir, Identifier: IRCT20190412043247N2. Registration Date: 6/13/2020. Registration timing: prospective.

**Supplementary Information:**

The online version contains supplementary material available at 10.1186/s12872-021-02131-1.

## Background

Diabetes mellitus (DM) is a chronic disease that is characterized by high blood glucose levels due to the inability to produce adequate amounts of insulin and/or resistance to the hormone’s actions [1]. Type 2 diabetes mellitus (T2DM) is a complex metabolic condition and, as the most common type of diabetes, it affects some 37% of the population in western and middle-eastern societies leading to long-term complications [2]. The major complications of this disease fall into two general categories of microvascular and macrovascular involvements, which can consequently lead to cardiovascular, neurological, ophthalmological, and renal damage [3]. Cardiovascular complications are the leading cause of death in the affected population. Atherosclerosis develops more rapidly in these patients and increases the incidence of a heart attack two to three times [4]. The management methods require multi-faceted strategies, including regular physical activity, proper diet, and medications to control hyperglycemia, hypertension, inflammation, and dyslipedemia [5, 6]. Among various medications available to treat diabetes, one of the newest ones is sodium-glucose co-transport 2 inhibitors (SGLT2-i) including empagliflozin, dapagliflozin, and canagliflozin. Empagliflozin is a selective inhibitor of the SGLT2 co-transporter expressed in the proximal tubule of nephrons. Inhibition of SGLT2 reduces hyperglycemia by decreasing glucose reabsorption in the kidneys leading to increased urinary glucose excretion, reductions in blood glucose and HbA_1C_ [7]. The EMPA-REG OUTCOME trial and its sub-studies revealed the additional beneficial effects of this medication versus standard treatment protocols in patients with T2DM and heart failure. These effects include a reduction in Major Adverse Cardiovascular Events (MACE), blood pressure, urinary albumin exertion, and improvements in lipid profile and vascular resistance [8, 9]. Some hypotheses have been advanced to explain the beneficial cardiovascular effects of this agent including hemodynamic changes due to decreased plasma volume following glycosuria-induced diuresis, changes in heart fuel consumption, improvements in overall metabolism by a reduction of inflammation, and direct effects on the cardiac tissue; however, the underlying mechanisms remain obscure [10, 11]. Many factors contribute to the physiopathology of cardiovascular complications in patients with T2DM including an increase in pro-inflammatory factors, imbalance in oxidative stress and a hyper-coagulation state with abnormal platelet function [12]. In this regard, animal models and in-vitro studies have been performed to evaluate the effects of empagliflozin on inflammatory state and platelet function. The results showed a reduction in oxidative stress, pro-inflammatory phenotype, and glucotoxicity, but platelet function remained unchanged [13, 14]. To date, few human model randomized trial has been performed to evaluate the inflammation and platelet dysfunction hypothesis in T2DM patients with coronary artery disease (CAD). Hence, the main objective of this parallel group, triple-blind randomized placebo-controlled trial is to test the hypothesis that empagliflozin improves the inflammatory state in T2DM patients with documented known CAD.

## Methods and experimental design

### Study design and Intervention

EMPA-CARD is a multicenter triple-blind randomized placebo-controlled trial designed to evaluate the effect of treatment with empagliflozin (10 mg tablet once daily) versus placebo for 26 weeks, in addition to standard care, in patients with T2DM and coronary artery disease.

#### Study objectives

The primary objective of the EMPA-CARD trial is to evaluate the effect of empagliflozin on the inflammatory state in patients with T2DM and coronary artery disease after 26 weeks of treatment (Fig. 1). Other objectives which will be investigated as the trial’s sub-studies are shown in Table 1.

**Fig. 1 Fig1:**
[figure not shown]
Pathways contributing to the development of micro- and macro-vascular complications in patients with T2DM and insulin resistance (only coronary artery disease, retinopathy and nephropathy are illustrated). Red boxes Indicate where the trial’s primary objective (potential molecular effects of empagliflozin on inflammatory state) will be assessed. The concept was derived from the studies of Bugger et al. and Oguntibeju et al. [15, 16]. *IL-6* interleukin 6, *IL-1* interleukin 1, *ROS* reactive oxygen species, *CRP* C-reactive protein, *GBM* glomerular basement membrane, *LDL* low density lipoprotein, *WBC* white blood cell, *PDGF* platelet derived growth factor, *TGF-β* transforming growth factor beta

**Table 1 Tab1:** Trial objectives and measurement methods (measured at time = 0 and after 26 weeks of treatment)

Objective	Definition
Primary	1. To investigate the impact of empagliflozin on plasma IL-6 level in patients with T2DM patients and coronary artery disease (established by coronary angiography)
Secondary	1. Inflammatory biomarkers Changes in serum hs-CRP levels Changes in plasma IL-1b levels 2. Oxidative stress status Changes in lymphocytic reactive oxygen species Changes in plasma levels of malondialdehyde Changes in plasma carbonyl levels Changes in plasma antioxidant capacity Changes in plasma reduced glutathione levels Changes in catalase enzyme activity Changes in plasma superoxide dismutase enzyme activity 3. Platelet function Changes in CD62-P expression on the platelet surface 4. Glycemic status Changes in fasting blood glucose levels Changes in HbA_1c_ levels Changes in HOMA-IR
Additional secondary (Considered for sub-studies)	1. Changes is cardiac biomarkers Changes in serum hs-Troponin I levels Changes in serum BNP levels Changes in serum NT-proBNP levels 2. Echocardiographic parameters Changes in left ventricular systolic function Changes in left ventricular diastolic function Changes in right ventricular function 3. Hematopoietic status and renal function Changes in serum erythropoietin levels Changes in blood hematocrit levels Changes in hemoglobin levels Changes in urine micro albuminuria levels 4. Changes in lipid profile Changes in serum total cholesterol levels Changes in serum LDL cholesterol levels Changes in serum HDL cholesterol levels Changes in serum triglyceride levels 5. Electrocardiographic parameters Changes in PR interval duration Changes in QRS complex duration Changes in QT interval duration Changes in ST segment deviation Changes in T wave alternans

*IL-6* Interleukin 6, *T2DM* type 2 Diabetes mellitus, *hs-CRP* high sensitive, *CRP* C-reactive protein, *IL-1b* interleukin 1-beta, *HbA*_*1c*_ glycated hemoglobin A_1c_, *HOMA-IR* Homeostatic Model Assessment for Insulin Resistance, *hs-Troponin I* high sensitive troponin I, *BNP* brain natriuretic peptide, *NT-proBNP* N-terminal pro-brain natriuretic peptide, *LDL cholesterol* low density lipoprotein cholesterol, *HDL cholesterol* high density lipoprotein cholesterol

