#### Trial population and eligibility assessment

Our goal is to randomize 100 participants from registries of 4 clinical centers (*i.e.,* Mousavi hospital (coronary angiography registry), Vali-e-Asr hospital, and two cardiology clinics of Zanjan University of Medical Sciences) in Zanjan, Iran. The pooled population of the clinics is 8000 patients, whose records were extracted from registries at the pre-recruitment phase. Patients aged between 45 and 75 years old with T2DM and known coronary artery disease (established by coronary angiography) who are on background standard anti-ischemic and anti-diabetic therapy with an HbA_1C_ between 6.5 and 9.5% were eligible for inclusion. The type and dose of background anti-diabetic medications should be constant for at least 3 months prior to recruitment. Patients’ left ventricular ejection fraction (LVEF) must be higher than 40%. Moreover, they must not be receiving anti-oxidant, anticoagulant, or antiplatelet medications or supplements (except for aspirin at 80 mg/d) for at least 3 months prior to recruitment. Detailed information for inclusion and exclusion criteria is provided in Table 2.

**Table 2 Tab2:** List of inclusion and exclusion criteria for randomization

Inclusion criteria	1. Age between 40 and 75 years 2. HbA1c between 6.5 and 9.5% 3. Documented known diabetes mellitus type 2 under continuous fixed-dose anti-diabetic treatment for at least 3 months prior to the randomization 4. Documented known coronary artery disease established by coronary angiography under continuous fixed-dose of anti-ischemic treatment for at least 3 months prior to the randomization 5. BMI less than 40 kg/m^2^ 6. Fixed diet and physical activity 7. eGFR greater than 45 ml/min/1.73m^2^ 8. Informed consent given in written form 9. Resting heart rate between 60 to 100 b/min

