Exclusion criteria	1. Pregnancy 2. Heart Failure (NYHA class 3–4) 3. Left ventricular ejection fraction < 40% 4. Use of anti-coagulant or anti-platelet drugs (except aspirin 80 mg/daily) for at least 3 months prior to the blood sampling 5. Consumption of alcohol, continuous anti-inflammatory drugs (except aspirin 80 mg/daily) or anti-oxidant supplement 6. Use of pioglitazone 7. History of allergic reaction to SGLT2-i medications 8. History of SGLT2-i medication usage 9. Gastrointestinal malabsorption disease 10. History of CABG, ACS, TIA, CVA or PCI during past 3 month 11. History or presence of malignancy 12. Severe HTN Resting systolic blood pressure ≥ 180 mmHg and/or Resting diastolic blood pressure ≥ 120 mmHg 13. Anemia (Hb < 10 g/dl) 14. Platelet count < 100,000/µl 15. History of infection during 1 one month prior to blood sampling 16. History of heart or lung transplant 17. Major psychiatric disorders 18. History of DKA 19. Elevated liver enzymes > 3 times upper normal limit 20. Use of drugs which prolong QT interval 21. Presence of arrhythmia 22. Electrolyte imbalance 23. Patients with pace maker

*HbA*_*1c*_ glycated hemoglobin A_1c_, *BMI* body mass index, *eGFR* estimated glomerular filtration rate, *NYHA* New York Heart Association, *SGLT2-I* sodium-glucose co-transporter-2 inhibitor, *CABG* coronary artery bypass graft, *ACS* acute coronary syndrome, *TIA* transient ischemic attack, *CVA* cerebrovascular accident, *PCI* percutaneous coronary intervention, *HTN* hypertension, *Hb* hemoglobin, *DKA* diabetic ketoacidosis

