#### Additional secondary outcomes

The additional secondary outcomes will be considered for the EMPA-CARD sub-studies including (1) Changes in cardiac biomarkers (Serum high-sensitive troponin I (hs-Troponin-I), brain natriuretic peptide (BNP) and N-terminal pro-brain natriuretic peptide (NT-proBNP) levels); (2) Changes in Echocardiographic parameters (left ventricular systolic and diastolic function and right ventricular function); (3) Changes in hematopoietic status and renal function (blood hematocrit, hemoglobin, and serum erythropoietin, and urine microalbuminuria levels); (4) Changes in lipid profile (serum total cholesterol, Low-Density Lipoprotein (LDL) cholesterol, High-Density Lipoprotein (HDL) cholesterol, and triglyceride levels); and (5) Changes in electrocardiographic parameters (PR interval duration, QRS complex duration, QT interval duration, ST-segment deviation, and T wave alternans).

All the above secondary outcomes will be assessed as the changes from baseline to week 26 of treatment in each study arm. Measurements of the biomarkers will be performed in the biotechnology laboratory of the Zanjan University of Medical Sciences and the Mousavi Hospital’s laboratory. The detailed information about the mentioned outcomes is presented in Table 4.

**Table 4 Tab4:** The detailed descriptions of selected outcomes

Outcome	Method of measurement	Mechanism	Time of measurement
Changes in plasma IL-6 and 1-beta levels	Plasma IL-6 and IL-1b Elisa kits	Key cytokines in development and maintenance of inflammation	Week 0 and 26
Changes in oxidative stress (Lymphocytic ROS, plasma MDA, Carbonyl, T-AOC, GSHr, CAT activity and SOD enzyme activity levels)	Flow cytometry (DCFDA as dye)^a^, spectrophotometry, colorimetric and FRAP assays	ROS, MDA and carbonyl increase in inflammation and causes cell damage GSHr, AOC, CAT activity and SOD activity increase in inflammation and reduce oxidative stress	Week 0 and 26
Changes in serum hs-CRP level	Turbidimetric assay	Circulating concentrations rise in response to inflammation	Week 0 and 26
Changes in platelet function^b^	Flow cytometry (MFI of CD62-P expression on platelet surface)	Platelet activity increases in DM and inflammation causing platelet dysfunction	Week 0 and 26
Changes in HbA_1c_, FBS and Basal Insulin level	Enzymatic assay	Indicate the glycemic status which is reduce with anti-glycemic drugs	Week 0 and 26

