Changes in HOMA-IR^c^	fasting insulin (mU/mL) × fasting glucose (mg/dL)/405	A method used to quantify insulin resistance which increases in DM and insulin resistance conditions	Week 0 and 26
Changes in serum hs-troponin I, BNP and NT-proBNP levels	Chemiluminescence assay	Specific cardiac biomarkers increase in cardiomyocyte damage and tension	Week 0 and 26
Changes in blood Hb, Hct and serum erythropoietin	CBC and serum erythropoietin Elisa kit	Reflects the hematopoietic status	Week 0 and 26
Changes in urine micro-albuminuria and albumin to creatinine ratio	Photometry and enzymatic assays	Reflects the renal and glomerular function. May increase in in DM as a microvascular adverse event	Week 0 and 26
Changes in lipid profile (serum TG, cholesterol, HDL,LDL cholesterols)	Enzymatic assay	Lipid disorders increase in DM which raises the cardiovascular complications that may decrease with empagliflozin treatment	Week 0 and 26
Changes in echocardiography parameters	2D trans-thoracic Echocardiography	Reflects left ventricular systolic and diastolic and right ventricular function	Week 0 and 26
Changes in electrocardiographic parameters	Electrocardiography	Reflects the electrophysiological activity of the heart	Week 0 and 26

*IL-6* interleukin 6, *IL-1b* interleukin 1-beta, *ROS* reactive oxygen species, *MDA* malondialdehyde, *T-AOC* total antioxidant capacity, *GSHr* reduced glutathione, *CAT* catalase, *SOD* superoxide dismutase, *DCFDA* dichlorofluorescin diacetate, *FRAP* fluorescence recovery after photobleaching, *hs-CRP* high sensitive C-reactive protein, *MFI* mean fluorescent index, *DM* diabetes mellitus, *HbA*_*1c*_ glycated hemoglobin, *FBS* fasting blood glucose, *HOMA-IR* homeostatic model assessment for insulin resistance, *hs-Troponin I* high sensitive troponin I, *BNP* brain natriuretic peptide, *NT-proBNP* N-terminal pro-brain natriuretic peptide, *Hb* hemoglobin, *Hct* hematocrit, *CBC* complete blood count, *TG* triglyceride, *HDL* high density lipoprotein, *LDL* low density lipoprotein cholesterol

^a^To assess the changes in ROS production, peripheral blood mononuclear cells (PBMC) will be separated from fresh whole blood and lymphocytes will be gated through sample acquisition in flow cytometric analysis

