#### Statistical analysis plan

We will use the means ± standard deviations (SD) and frequencies and percentages n (%) to interpret the results. The noninferiority margin and 95% confidence interval (CI) will be estimated for primary outcomes. The noninferiority will be accepted if the upper 95% CI for the relative risk (RR) lies below the margin of noninferiority. An intention-to-treat analysis will be used to examine the effect of missing data. Superiority analysis will be performed at α = 0.05 level. The interaction effects will be examined using graphical and statistical tests. The Kolmogorov–Smirnov test will be used to determine the normality of the distribution of continuous quantitative data. Independent T-test will be used (on condition of normal distribution) for statistical analysis of quantitatively continuous variables findings related to primary and secondary outcome including interleukin 6 levels, oxidative stress biomarkers, platelet function, glycemic status, cardiac biomarkers, echocardiographic finding, hematopoietic and renal biomarker, lipid profile and electrocardiographic parameters. The Mann–Whitney U test will be used on the condition of abnormal distribution. Chi-square test will be used to analyze qualitative data such as ST segment deviation and T-wave changes in electrocardiogram. We will consider the probability of 0.05 for the main analysis. We will perform Bayesian analysis of the covariance test to examine the effects of intervention on IL-6. The primary outcome is considered as confirmatory and the secondary outcomes are considered as exploratory. All statistical tests will be carried out in the in Rv.4 environment. The primary data of the FFQ will be evaluated by using the Nutritionist software version 4 (N4).

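### The exploratory ECG outcome is named as plain QT interval duration, with no heart-rate correction or heart-rate covariate, so its change also carries any change in heart rate

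*Protocol article*

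**What the plan says.** Two places in the protocol article define the outcome. Table 1, under the additional secondary objectives, item 5, lists "Changes in QT interval duration". The section on additional secondary outcomes gives the ECG set as "PR interval duration, QRS complex duration, QT interval duration, ST-segment deviation, and T wave alternans". Neither mentions a rate correction. The ECG row of Table 4 gives electrocardiography as the method and says of the outcome only "Reflects the electrophysiological activity of the heart". The abbreviation list has no entry for a corrected QT.

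The contrast and the test are also stated. On timing: "All the above secondary outcomes will be assessed as the changes from baseline to week 26 of treatment in each study arm". The statistical analysis plan section says "Independent T-test will be used (on condition of normal distribution) for statistical analysis of quantitatively continuous variables findings" and includes electrocardiographic parameters among those variables, with the Mann-Whitney test if the data are not normal. The only covariance analysis named is the Bayesian one for IL-6. Heart rate is not a listed outcome.

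Two eligibility items in Table 2 bear on the point: inclusion item 9, "Resting heart rate between 60 to 100 b/min", and exclusion item 20, "Use of drugs which prolong QT interval".

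**The concern.** The QT interval depends on the heart rate at the moment of recording. A change in raw QT between two visits therefore combines a change in repolarisation with a change in rate. The article fixes the variable, the contrast and the test. Followed literally, these compare the arms on the combined quantity, with nothing to separate its two parts.

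This has two consequences. First, if heart rate drifts between visits in the same way in both arms, the QT change is noisier than it need be. Second, if treatment itself alters heart rate, the arms would differ in raw QT without any repolarisation effect, or a real effect could be masked. The Background section attributes haemodynamic effects to the drug (lower blood pressure and, as a hypothesis, reduced plasma volume). A rate effect thus cannot be excluded in advance, but none is reported. Because heart rate is not a listed outcome, a reader of the results might not be able to tell which part had moved.

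**Working it through.** The article gives no QT effect size, standard deviation or power statement, so there is no figure of its own to reproduce. The calculation below is an illustration and its assumptions are labelled.

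**Inputs**
- Heart rates of 70 and 75 b/min: assumed. Both lie inside the 60 to 100 b/min allowed at entry (Table 2).
- Corrected QT of 400 ms, held constant: assumed.
- Standard correction relations, with RR = 60/HR in seconds: Bazett, QT = QTc × RR^(1/2); Fridericia, QT = QTc × RR^(1/3).
- 41 patients per arm: the required number in the sample size section, before the dropout allowance.

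**Step 1. Effect of an assumed 5 b/min shift on raw QT**

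| | 70 b/min | 75 b/min | Change |
|---|---|---|---|
| Bazett | 400 × (60/70)^(1/2) = 370.3 ms | 400 × (60/75)^(1/2) = 357.8 ms | about −12.5 ms |
| Fridericia | 400 × (60/70)^(1/3) = 380.0 ms | 400 × (60/75)^(1/3) = 371.3 ms | about −8.6 ms |

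Raw QT moves by about 9 to 13 ms with no change in repolarisation.

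**Step 2. Slope near 75 b/min**

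Differentiating the relations gives a slope of QT/(2 × HR) for Bazett and QT/(3 × HR) for Fridericia.
- Bazett: 357.8/150 = 2.4 ms per b/min.
- Fridericia: 371.3/225 = 1.7 ms per b/min.

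Each 1 b/min difference between arms in heart-rate change would therefore shift the raw QT contrast by about 1.7 to 2.4 ms.

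**Step 3. Noise when treatment does not affect heart rate**

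Assume that the within-patient change in heart rate has a standard deviation of 5 to 10 b/min.
- Contribution of rate to the SD of the QT change: 1.65 × 5 = 8 ms at the low end, 2.4 × 10 = 24 ms at the high end.
- Contribution to the standard error of the between-arm difference with 41 per arm, using SD × √(2/41) = 0.22 × SD: about 2 to 5 ms.

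**Step 4. What the plan does about it**

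The 60 to 100 b/min criterion applies at entry and is not a condition of the week 26 ECG. The stated tests are unadjusted. Nothing in the article removes the rate component.

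**The case against.** The strongest reply is that a journal article uses short labels. Left ventricular systolic function has no metric either, all ECG parameters share one row of Table 4, and a trial procedure manual exists that is not shown. A correction formula could sit there, and the article does not say that correction is ruled out. This stands as a reason for modest weight. It does not dispose of the point, because the article states the variable, the contrast and the test, and the variable stated is plain QT. If a fuller document uses a corrected QT, the published definition should match it.

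Randomisation and blinding also count for something. Rate variation common to both arms is noise, not bias. Table 2 excludes arrhythmia, pacemakers, electrolyte imbalance and QT-prolonging drugs, and requires fixed-dose anti-ischaemic treatment before entry. All of this narrows the problem.

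A reader might go further and infer that the outcome largely measures heart rate. The documents do not support that, because they give no standard deviation for heart rate or QT. Under assumed values (mean heart rate 75, SD 5 to 12 b/min, truncated to 60 to 100; mean corrected QT 420 ms, SD 15 to 25 ms), heart rate explains 24 to 74% of between-patient variance in raw QT with Bazett and 12 to 56% with Fridericia. It is a majority only under some of these assumptions, and the share concerns QT itself, not its change.

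A reader might also cite the spread across the whole entry range. At a corrected QT of 400 ms, raw QT at 100 b/min is 310 ms (Bazett) or 337 ms (Fridericia), which is 90 or 63 ms below the value at 60 b/min. That compares different patients, whereas the outcome is a within-patient change, from which stable differences between patients largely drop out.

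**Conclusion.** The point holds in limited form. As written, the outcome is the change in uncorrected QT, tested without a heart-rate covariate. Heart-rate variation between visits adds noise to it, and any treatment effect on heart rate would pass into it at about 1.7 to 2.4 ms per b/min near 75 b/min. The 9 to 13 ms illustration rests on an assumed 70 to 75 b/min shift and a corrected QT of 400 ms. Neither figure comes from the trial.

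It does not follow that the between-arm QT comparison is biased. Bias needs a treatment effect on heart rate, and the document reports none. Nor is QT the only listed item that touches repolarisation, since ST-segment deviation and T wave alternans are in the same set.

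Importance is low. QT is one of 19 additional secondary items intended for sub-studies, secondary outcomes are declared exploratory, and neither the IL-6 analysis nor the sample size is affected.

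**What to change.** In Table 1 and in the section on additional secondary outcomes, define the outcome as change from week 0 to week 26 in heart-rate-corrected QT. Name one formula before unblinding, for example Fridericia, with RR taken from the same ECG. Report change in heart rate by arm beside it and keep raw QT as descriptive only. Naming the formula in advance also prevents a later choice among raw QT, Bazett and Fridericia.

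No new data are needed, because RR is on the same tracing. The cost is one line of computation and a wording change in two places. Sample size, power and alpha are unchanged.
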